# Clinical trial protocol of the ASTER trial: a double-blind, randomized, placebo-controlled phase III trial evaluating the use of acetylsalicylic acid (ASA) for enhanced early detection of colorectal neoplasms

**DOI:** 10.1186/s12885-018-4826-3

**Published:** 2018-09-24

**Keywords:** Colorectal cancer, Early detection, Screening, Acetylsalicylic acid, Sensitivity, Specificity

## Abstract

**ᅟ:**

Immunochemical fecal occult blood tests (iFOBTs) are increasingly used for colorectal cancer (CRC) screening. In our preceding observational study, sensitivity for detecting advanced colorectal neoplasms by iFOBT was 70.8% among users of low-dose acetylsalicylic acid compared with 35.9% among non-users (*p* = 0.001), whereas there were only very small differences in specificity. In receiver operating characteristics (ROC) analyses, the area under the curve (AUC) was much higher for acetylsalicylic acid users than for non-users, with particularly strong differences in men (0.87 versus 0.68, *p* = 0.003). These findings suggested that use of acetylsalicylic acid before conduct of iFOBT might be a promising approach to improve non-invasive screening for CRC.

**Methods/design:**

In this randomized, double-blind, placebo-controlled trial, the diagnostic performance of two iFOBTs for detecting advanced colorectal neoplasms after a single low-dose of acetylsalicylic acid (300 mg) compared to placebo is evaluated. Acetylsalicylic acid or placebo is administered at least 5 days before a planned, study-independent colonoscopic screening in 2400 participants aged 40 to 80 years. Stool samples are obtained before and on three different days after the single dose of acetylsalicylic acid or placebo. In addition, optional blood samples are taken for future biomarker analyses. The diagnostic performance of the iFOBTs will be compared to the results of the colonoscopy as a gold standard for the diagnosis of colorectal neoplasms. Additionally, gender-specific performance of the tests and gain in diagnostic performance by test application on multiple days will be evaluated.

**Discussion:**

If the findings from our preceding observational study will be confirmed in this large trial, the proposed low-risk, inexpensive intervention would considerably improve the diagnostic accuracy of iFOBTs and thus lead to enhanced early detection of colorectal neoplasms. Thus, the results of this trial may have a large public health impact.

**Trial registration:**

This trial was registered before recruitment of the participants in www.clinicaltrialsregister.eu on the 30th of May 2012: EudraCT No.: 2011–005603-32 and in www.drks.de on 13th of March 2012: German Clinical Trials Register DRKS-ID: DRKS00003252.

**Electronic supplementary material:**

The online version of this article (10.1186/s12885-018-4826-3) contains supplementary material, which is available to authorized users.

## Background

Colorectal cancer (CRC) is the third most common cancer and the fourth most common cancer cause of death globally, with more than 1.3 million new cases and more than 700,000 deaths annually [1]. In Germany, there are over 60,000 new cases and around 25,000 deaths due to CRC per year [2]. The commonly slow progression from detectable and fully curable precursors (adenomas) to still-curable early-stage CRC to advanced CRC provides promising perspectives for prevention and early detection by screening.

Randomized studies have demonstrated that CRC incidence and CRC-associated mortality can be reduced by 20–30% through annual or biennial screening with fecal occult blood tests (FOBTs) [3–5], despite the low sensitivity for detection of colorectal adenomas of conventional (guaiac based) FOBTs. Substantially higher sensitivity for detection of colorectal adenomas can be achieved with newer, immunochemical FOBTs (iFOBTs), which are increasingly recommended and employed for non-invasive CRC screening. Although iFOBTs detect approximately four out of five CRCs [6], the sensitivity for detecting advanced adenomas, the precursors of most CRCs, still remains far below 50% at cut points yielding 90–95% specificity required for population-based screening. Thus, there is an unmet medical need for easy-to-implement screening methods for detection of high-risk colorectal adenomas in addition to CRC.

In our preceding prospective screening study conducted among 1979 participants of screening colonoscopy in Germany, the sensitivity for detecting advanced colorectal neoplasms (i.e. either CRC or advanced adenoma) by iFOBT was 70.8% among users of low-dose acetylsalicylic acid compared with 35.9% among non-users (*p* = 0.001), whereas there were only very small differences in specificity (85.7% for users compared with 89.2 to 91.1% for non-users) [7]. In receiver operating characteristics (ROC) analyses, the area under the curve (AUC) was much higher among users than among non-users, with differences being particularly pronounced among men (0.87 versus 0.68, *p* = 0.003). This suggests that use of acetylsalicylic acid prior to conduct of iFOBT might be a particularly promising approach for enhancing non-invasive screening for CRC. It is hypothesized that the underlying mechanism could be an enhanced tendency of (micro-)bleeding of colorectal neoplasms.

### Objectives

The main objective of this trial is to evaluate the diagnostic performance (sensitivity, specificity, positive and negative predictive values, likelihood ratios, and AUC of two iFOBTs for detecting advanced colorectal neoplasms after a single dose of acetylsalicylic acid as compared to placebo.

Secondary objectives are: 1) To study gender-specific performance of the two iFOBTs and the possible gain in diagnostic performance by stool sampling on multiple days; 2) To study the safety of single-dose acetylsalicylic acid in the selected population; 3) To collect blood samples for additional biomarker analyses (optional).

## Methods/Design

### Study design

This trial is designed as a randomized, double-blind, placebo-controlled, phase III multicenter trial (German title: ‘Mit **AS**S Darm**t**umore früher **er**kennen’, acronym ASTER).

### Screening

In total, 2400 eligible participants aged 40 to 80 years and with no recent use of acetylsalicylic acid are recruited when visiting one of the collaborating gastroenterology private practices or hospitals (hereinafter referred to as ‘study centers’) for an informative appointment, which is routinely scheduled a few weeks before colonoscopy. The study flow of the trial is illustrated in Fig. 1. The exact schedule can be found in Table 1. In addition to participants scheduled for a screening colonoscopy, patients visiting the study centers for a diagnostic colonoscopy meeting the inclusion criteria are also asked to participate. Thus, the colonoscopy procedure is planned beforehand and conducted independently from our trial.

**Fig. 1 Fig1:**
[figure not shown]
Overview of study flow

**Table 1 Tab1:** Study schedule

Trial-specific procedures	Screening	Baseline	Treat-ment	Observation			Post-study
Timeline			Day 0	Day 2	Day 3	Day 4	Colonoscopy from day 5 onwards
Informed consent	X						
Inclusion/ exclusion criteria	X						
Randomization	X						
Physical examination	X						
Patient parameters^a^	X						
Blood sampling for biomarker analyses (optional)^e^	X						
Questionnaire^b^	X						
Handing over stool collection material and subject diary^c^	X						
Drug administration (Acetylsalicylic acid or placebo)			X				
Stool sample^d^ (FOBGold®Tube Screen)		X		X	X	X	
Stool sample^d^ (FD Hb/Hp Complex)		X		X	X	X	
Concomitant therapy recording			X	X	X	X	
(S)AE recording^f^			X	X	X	X	

^a^Age, sex, weight, height, and blood pressure

^b^The questionnaire includes questions on family history of CRC and lifestyle factors such as smoking and alcohol consumption

^c^Eight kits are handed over

^d^If stool collection on these days is not possible because of constipation or other reasons, stool collection may be postponed to the subsequent days; participants are also allowed to collect only two stool samples, which should be at baseline (without medication) and on day 2, if possible

^e^Blood sampling for biomarker analysis: 2 EDTA tubes; 2 serum tubes

^f^Interview of participants before colonoscopy

During the first appointment (day of Screening), participants are informed about the trial, receive the printed study information, and have the opportunity to ask questions. A detailed medical and drug history is taken and inclusion and exclusion criteria are checked (see the full list of inclusion and exclusion criteria for details in Appendix). Women who are not postmenopausal must have a negative pregnancy test before signing consent. If all inclusion criteria are met, no exclusion criteria are present, and the patient consents to the blood sampling, four extra tubes of blood (2 EDTA tubes and 2 serum tubes) are taken for analysis of additional biomarkers (optional). In addition, patients receive four iFOBT kits for each of two different iFOBTs (FOBGold®Tube Screen, an internationally widely used quantitative iFOBT [8, 9], as well as the FD Hb/Hp Complex quick test, a qualitative chromatographic test from Frost Diagnostika; hence, eight stool kits in total are dispensed along with instructions on when and how to use them and including a device that is hung in the toilet and aids in easy collection of the stool samples.

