### Participants’ information

To ensure adherence to the study medication, participants are instructed in detail before start of the trial. Given that the medication scheme includes only one single dose of study drug, no major problems in taking the medication is expected. All participants receive a participant diary in which they document if and when they took the study medication, and if and when they collected the stool samples. The participant sends this diary to the coordinating center in Heidelberg using a prepaid envelop. Finally, participants are asked to fill out a standardized questionnaire addressing potential determinants of risk of colorectal neoplasms and of test performance, including general participant characteristics, co-morbidities, and lifestyle factors. They can either do this during their visit to the study center or at home.

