### Safety assessment

Participants are asked about concurrent use of medication and diseases at inclusion to minimize the risk of AEs. Candidate participants in the trial are excluded if they use potentially interacting medications or have illnesses that may be worsened by participation in this trial. In the patient information documents, participants are informed about all relevant potential AEs that may occur. Furthermore, participants are instructed to contact their general practitioner or the investigator in the unlikely case of a severe medical problem.

The observation period for AEs is defined as day 0 to day 4 for this trial. When the participants come for the scheduled study-independent colonoscopy, they are asked about any potential AEs or events potentially related to the use of the medication. All AEs are documented and the investigator judges intensity, seriousness, and relatedness of an AE using standard criteria. This information is documented in a standardized way in the eCRF. All serious AEs (SAEs) must be reported within 24 h, or on the next working day at the latest, using a standardized SAE report form.

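### Non-serious adverse events for days 0 to 4 rest on one later recall interview with no stated latest date; the diary kept on those days could serve as a cheap same-day record

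*Protocol article*

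**What the plan says.** All references are to the protocol article.

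- **Window.** Safety assessment: "The observation period for AEs is defined as day 0 to day 4 for this trial".
- **Method.** Table 1 marks adverse-event recording on days 0, 2, 3 and 4, and footnote f on that row reads "Interview of participants before colonoscopy". Safety assessment agrees: when participants come for colonoscopy, "they are asked about any potential AEs or events potentially related to the use of the medication".
- **Timing of the interview.** The last column of Table 1 is headed "Colonoscopy from day 5 onwards". The Colonoscopy section sets a minimum of 5 days after the dose. Neither place gives a maximum.
- **Diary.** Participants' information describes a "participant diary in which they document if and when they took the study medication, and if and when they collected the stool samples". It is posted to the coordinating center. Adverse events and other medicines are not among the contents listed.
- **Other drugs.** Table 1 has a row "Concomitant therapy recording" marked on the same four days. It carries no footnote. The only stated questioning about other medication is at inclusion.
- **Severe events.** Safety assessment tells participants to contact their general practitioner or the investigator about a severe problem. Serious events must be reported within 24 hours or on the next working day.
- **Analysis set.** Statistical analysis places all randomized patients in the safety analysis, whether or not a colonoscopy report exists.

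**The concern.** Table 1 can be read as showing data recorded day by day, but for adverse events the stated source is one conversation after the window has closed. Dyspepsia, minor bleeding or other brief complaints after a single tablet are the events most easily forgotten or misdated. The participant already has a form to complete at home over those days, and as described it does not ask about them.

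Safety is a named secondary objective. Participants have no individual benefit from the dose, and the intended use is screening of a broad population, so the argument depends on the intervention being low-risk. If mild events are under-recorded, a true absolute excess in the active arm looks smaller and is estimated less precisely. Participants who do not come to colonoscopy could enter the safety denominator without ever having been asked.

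**Working it through.** The protocol gives no figure to reproduce here. The check compares its statements and adds one illustration.

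**1. Recall interval.** For an event on day d (0 to 4) and an interview on day k (5 or later), the lag is k − d days.

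- Earliest interview, k = 5: the lag is 5 days for a day 0 event and 5 − 4 = 1 day for a day 4 event.
- General k: the lag runs from k − 4 to k days. No upper limit on k is stated, so the longest lag has none either.

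**2. Table against text.** The window in Safety assessment covers five days (0, 1, 2, 3, 4). Table 1 has columns for four of them and none for day 1. The text controls the window, so a day 1 event still counts. This is a mismatch to tidy, not a gap in coverage.

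**3. Who is asked.** The stated interview is tied to attendance at colonoscopy, while the safety set is everyone randomized. For a participant who does not attend, only the severe-problem route is stated. The documents do not say how many participants this will be. The 20% loss of data in the sample size section is not broken down by cause.

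**4. Illustration of under-recall.** Assumptions, none from the protocol: true event rates of 5% and 3%, the same recalled fraction r in both arms, and all 1200 per arm (2400 / 2) interviewed. The test is two-sided at 0.05.

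With p1 = 0.05r, p2 = 0.03r and p = (p1 + p2)/2:

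power = Φ{[p1 − p2 − 1.96·√(2p(1−p)/n)] / √[(p1(1−p1) + p2(1−p2))/n]}

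At r = 1: (0.02 − 1.96 × 0.00800) / 0.00799 = 0.541, and Φ = 0.706.
At r = 0.5: (0.01 − 1.96 × 0.005715) / 0.005712 = −0.21, and Φ = 0.417.

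| Recalled | Rates | Difference (points) | Risk ratio | Power |
|---|---|---|---|---|
| 100% | 5.0% vs 3.0% | 2.0 | 1.67 | 71% |
| 80% | 4.0% vs 2.4% | 1.6 | 1.67 | 61% |
| 60% | 3.0% vs 1.8% | 1.2 | 1.67 | 48% |
| 50% | 2.5% vs 1.5% | 1.0 | 1.67 | 42% |

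The risk ratio does not move, but its precision does. With expected counts a and b, the standard error of the log risk ratio is √(1/a + 1/b − 2/n).

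- Full capture (60 vs 36 events): 0.207, so the 95% interval around 1.67 is 1.11 to 2.50.
- Half recalled (30 vs 18 events): 0.295, so the interval is 0.93 to 2.97.

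**The case against.** The strongest reply is that nothing is hidden. Footnote f names the interview, the text repeats it, and the ticks in Table 1 can be read as the period covered. One blinded interview is an ordinary choice for a single-dose trial. This stands: the point is a weakness of method, not a contradiction. Disclosure does not, however, limit how late the interview may be.

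The illustration is also open to challenge. Only the primary endpoints are confirmatory, no adverse-event comparison is powered, and the rates and recall fractions are assumed. This stands too, so the table shows a direction and a rough scale and says nothing about the protocol's own properties.

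Four stronger readings are tempting and are not supported:

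- **That concomitant drugs come from the same recall interview, so that forgotten painkiller use would affect the day 2 primary analysis.** Footnote f is not on that row, and the stated interview question concerns adverse events and medication-related events. The source of post-dose drug data is unstated, which is a different matter.
- **That the schedule skips the first day after dosing.** Day 1 lies inside the stated window.
- **That recall routinely spans weeks.** The appointment is "routinely scheduled a few weeks before colonoscopy", but that interval runs from the appointment and not from the dose. An interview on day 5 fits the text equally well.
- **That the diary certainly omits complaints and other medicines.** The form is not shown, and a condensed article describes it in one sentence. Only the listed contents can be relied on.

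**Conclusion.** The concern holds in a narrow form. Non-serious adverse events for days 0 to 4 are routinely obtained from one interview at the colonoscopy visit. The minimum recall is 1 to 5 days, no latest date is stated, and no interview is stated for participants who do not attend although they are in the safety set. Severe problems have their own prompt route.

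The likely harm is a smaller absolute difference and lost precision for mild events. With equal recall in blinded arms, the risk ratio is not biased. The size cannot be fixed from the documents. Under the assumed rates, halving recall takes the difference from 2.0 to 1.0 points and power from 71% to 42%. The primary endpoint is not shown to be affected. This is a cheap improvement of minor weight.

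**What to change.** Add to the existing diary, for each of days 0, 1, 2, 3 and 4, one line for any complaint and one for any medicine taken. If the full diary form already has these lines, the protocol should say so.

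Have the participant bring the diary to the pre-colonoscopy interview as a memory aid, so that the investigator can grade and attribute each entry before it is posted. Ask participants who miss colonoscopy to return it as well. Name the diary as the source of the concomitant-therapy row, and add day 1 to Table 1 so that it matches the window in Safety assessment.

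The cost is two lines per day on a form that is already scanned, verified and checked for plausibility. The downsides are slightly more data entry, more minor events reported in both arms, and somewhat later arrival of diaries at the coordinating center.

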### Study medication

Participants are randomized to receive either a single dose of 300 mg acetylsalicylic acid (without enteric coating, Ratiopharm GmbH) or placebo (containing cellulose, lactose and magnesium stearate; Winthrop Arzneimittel GmbH); thereby, a unique participant number is generated and documented on the day of screening in the participants’ log.

Both, participants and their physicians are blinded with respect to the study medication.

### Stool collection

Participants are asked to collect a baseline stool sample before taking the study medication. If the participant cannot collect a stool sample at baseline (e.g. due to constipation), this stool sample is skipped and the study medication is taken without a baseline stool sample. Further stool samples are collected from day 2 onwards on 3 different, preferably consecutive days (day 2, 3, and 4). If stool collection on these days is not possible because of constipation or other reasons, stool collection may be postponed to the subsequent day. Participants are still eligible for inclusion in the analysis if they only provide two stool samples (before taking study medications and on day 2, if possible). At each time point at which stool samples are collected, one kit of each test is used and the actual day documented. The stool sampling devices ensure collection of defined volumes of stool which are given to a buffer that hinders degradation of hemoglobin (for example FOBGold®Tube Screen test: 10 mg stool in 1.7 ml buffer). All stool samples are collected at the participants’ homes and prior to initiation of large bowel preparation for colonoscopy. The stool samples are stored in the refrigerators and sent by mail to the coordinating center (Heidelberg) using special pre-paid and addressed mailing devices.

### Participants’ information

To ensure adherence to the study medication, participants are instructed in detail before start of the trial. Given that the medication scheme includes only one single dose of study drug, no major problems in taking the medication is expected. All participants receive a participant diary in which they document if and when they took the study medication, and if and when they collected the stool samples. The participant sends this diary to the coordinating center in Heidelberg using a prepaid envelop. Finally, participants are asked to fill out a standardized questionnaire addressing potential determinants of risk of colorectal neoplasms and of test performance, including general participant characteristics, co-morbidities, and lifestyle factors. They can either do this during their visit to the study center or at home.

### Colonoscopy

The colonoscopy is planned and conducted in the setting of screening for CRC or diagnostic workup and, as such, it is not part of the trial. However, the investigator must ensure that there are at least 5 days (4 full acetylsalicylic acid-free days) between taking the study medication and the colonoscopy. Although a single dose of acetylsalicylic acid is not considered a contraindication for elective colonoscopy, this time interval was chosen to minimize any possibility of an increased risk of bleeding at colonoscopy or endoscopic removal of small polyps [10–12]. However, the findings from screening colonoscopy are collected and used in the analysis.

Colonoscopy (and histology) reports are de-identified (i.e. any personal data is removed and the participant number is noted) and sent from the study centers to the coordinating center (Division of Clinical Epidemiology and Aging Research at the German Cancer Research Centre, Heidelberg).

### Data collection and documentation in recruiting centers

For each participant in the clinical trial written informed consent is obtained before enrollment into the trial, which is stored by the investigator in the investigator site file (ISF) at study centers for at least 10 years after the end of the trial.

All participants’ data collected at the study centers are entered into the electronic Case Report Form (eCRF) by the study physicians and physician assistants on site. Data collected in the eCRF includes: participant number (available once a patient is randomized); participant’s medical history, and data collected during physical examination; verification of compliance with inclusion and exclusion criteria; dates of participation in the trial, including date of informed consent, dispensing of study material, and date of colonoscopy; information on whether an optional blood sample was taken; laboratory values (thrombocytes) if available from clinical routine; adverse events (AEs); protocol violations; date of drop-out and reasons, if applicable.

The eCRF does not contain the participant’s identifying information, but only his/her participant number. Entries in the eCRF may only be made by the investigator or persons authorized by him. If corrections in the eCRF are necessary, the initial entry will be kept in an electronic log (audit-trail). A list is kept of the individuals who are authorized to make data changes. At the end of the trial, data collected in the eCRF are transferred digitally into a database at the coordinating center in Heidelberg.

To confirm adherence to the study medication, the participants are asked to bring the empty package of the study medication when coming to the planned colonoscopy. Information on medication usage is collected in a drug accountability log.

